### Incentives

All participants will receive US $30 for completion of the baseline survey and an additional US $30 after completing each of the follow-up surveys. Incentives will be given via email in the form of gift cards to an online retailer, such as Amazon.

### Sample Size

The research team proposes to enroll and maintain a sample of 200 TY aged 15-24 years. In order to achieve this target, recruitment efforts will continue until approximately 250 TY are enrolled. Allowing for 20% loss to follow-up, this approach will produce a sample of 200 TY who are expected to complete the prospective pilot RCT. As a comparison, an ongoing RCT of couples’ HIV counseling and testing in MSM [44] has a retention rate of 90-95%, making a 20% loss-to-follow-up a generous allowance. The sample size is calculated based on the detection of significant changes in each of the outcomes between the control and intervention groups. If data are pooled across participants’ gender identities, the study will have 81%, 92%, and 99% statistical power to observe differences of 10%, 12%, and 15% in the primary outcomes, respectively.

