**Objective:**

Project Moxie involves a pilot randomized controlled trial (RCT) of 200 TY aged 15-24 years, who are randomized on a 1:1 basis to control or intervention arms. The aim is to examine whether the addition of counseling provided via telehealth, coupled with home-based HIV testing, can create gains in routine HIV testing among TY over a six-month follow-up period.

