**Methods:**

This study implements a prospective pilot RCT of 200 TY recruited online. Participants in the control arm will receive one HIV self-testing kit and will be asked to report their results via the study’s website. Participants in the experimental arm will receive one HIV self-testing kit and will test with a remotely-located counselor during a prescheduled video-counseling session. Participants are assessed at baseline, and at three and six months posttesting.

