Another important limitation of the current telehealth literature concerns its use as an information dissemination and case management tool. Few studies use this technology for actual clinical care, such as HIV testing. With approval by the US Food and Drug Administration in 2011, high quality (sensitivity 93.64%, 95% CI 82.46-98.66; specificity 99.87%, 95% CI 99.28-100.00 [20]), home-based HIV testing is now available commercially in all 50 states [21]. However, critiques of home-based HIV testing include difficulty interpreting the results, a lack of posttest counseling for the adoption of safer HIV prevention methods, and a lack of proper linkage to care [22]. Adding online counseling through video-chat software to home-based HIV testing has the potential to mitigate these concerns. Through telehealth-delivered counseling, individuals can receive tailored, convenient, and confidential support that due to stigma, discrimination, and/or lack of locally-available services, may not otherwise be received. While there are few telehealth-based HIV prevention interventions published in the literature, results from prior studies show increased knowledge, self-efficacy, and motivation towards effective HIV prevention methods [23-26].

This paper describes the protocol for the first study to combine telehealth and home-based HIV testing for comprehensive, gender-affirming HIV testing and counseling for TY. In this study, approximately 200 TY aged 15-24 years will be randomized into either a control group that receives an HIV self-testing kit or an intervention group that receives an HIV self-testing kit as well as a video-chat counseling session provided by a trained HIV counselor. The main outcome of this study is the frequency of HIV testing in the six months following initial testing. The study aims to examine whether the receipt of an HIV self-testing kit plus a video-chat-delivered counseling session can create changes in HIV testing behavior, sexual risk-behaviors, and linkage to care for newly-diagnosed HIV-positive TY. If successful, this low-cost intervention has the potential to shape the delivery of HIV prevention and care services to this population, who are currently overlooked in HIV programming, research, and prevention efforts.

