## Methods

### Study Overview

This study is a pilot randomized controlled trial (RCT) of 200 self-identified TY aged 15-24 years, recruited via a range of social media platforms. Participants will be randomized to one of two study arms. TY in the control arm will receive one HIV self-testing kit by mail and will be asked to report their results via a study website. TY in the experimental arm will also receive one HIV self-testing kit via mail, and will conduct this test under the supervision of a remotely-located counselor during a prescheduled video-chat session. Participants in both arms will complete a baseline survey upon recruitment, with repeat surveys at three and six months posttesting (see Figure 1). Participants will receive email and SMS reminders to log into the study website to complete follow-up surveys. The primary outcome for this study is routine HIV testing during the follow-up period. Secondary outcomes include sexual risk-taking behaviors, intervention acceptability, and linkage to care for those who test positive for HIV.

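### The Abstract and Introduction randomise about 200, while Sample Size enrols about 250 so that 200 complete; 200 cannot be both the number randomised and the number completing

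*Protocol article*

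**What the plan says.** Five places in the article give the size of the trial.

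- Abstract, Objective: a "pilot randomized controlled trial (RCT) of 200 TY aged 15-24 years, who are randomized on a 1:1 basis".
- Abstract, Methods: "This study implements a prospective pilot RCT of 200 TY recruited online".
- Introduction, last paragraph: "approximately 200 TY aged 15-24 years will be randomized into either a control group" or an intervention group.
- Methods, Study Overview: "This study is a pilot randomized controlled trial (RCT) of 200 self-identified TY aged 15-24 years".
- Methods, Sample Size: "The research team proposes to enroll and maintain a sample of 200 TY aged 15-24 years", followed by the statement that "recruitment efforts will continue until approximately 250 TY are enrolled". It allows for 20% loss to follow-up, expects 200 to complete, and then gives power of 81%, 92% and 99% for differences of 10%, 12% and 15%.

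The Objective and the Introduction attach 200 explicitly to randomisation. The Abstract's methods and the Study Overview give only a trial size. The Study Procedure section places randomisation (1:1) after consent, screening, registration and the baseline survey.

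**The concern.** The figure 200 carries two meanings: participants randomised, and participants left at the end of follow-up. These differ by the plan's own loss allowance. The number randomised tells the team when recruitment may end and tells the reader which sample the power refers to. Recruitment was still open when the article was written, with 130 enrolled, so the question was not academic.

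The larger figure is also counted in a loose unit. The 250 are enrolled, but the procedure has several steps between entering the study and being randomised. The article therefore never states plainly how many will be randomised to reach 200 completers.

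**Working it through.** **Inputs.** About 200 randomised (Objective, Introduction); about 250 enrolled, 20% loss, 200 completing and power of 81/92/99% (Sample Size); 90-95% retention in an ongoing couples' testing trial (Sample Size); 1:1 allocation (Study Procedure). Alpha, sidedness and the control-arm testing rate are not given, so every two-arm power figure below rests on assumptions.

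**1. The plan's own inflation.** Enrolment needed = completers / (1 - loss) = 200 / (1 - 0.20) = 250. In reverse, 250 x 0.80 = 200. The figure reproduces exactly.

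**2. Can both statements hold?** If 200 are randomised and 20% are lost, completers = 200 x 0.80 = 160, which is 40 fewer than the 200 that Sample Size expects. Suppose instead that 250 register and 200 of them are randomised. That does not help: Sample Size attributes the fall from 250 to 200 to loss to follow-up and describes the 200 as completing the trial. No reading of the enrolment order makes the two agree.

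**3. Size of the shortfall if recruitment stopped at 200 randomised.**

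- 20% loss: 160 completers, about 80 per arm.
- 10% loss: 200 x 0.90 = 180.
- 5% loss: 200 x 0.95 = 190.

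**4. Which sample the printed power refers to.** The power sentence follows the 200 completers without naming a sample. A one-group two-sided 5% z-test with standard error 0.5/sqrt(N), power = Phi(d/SE - 1.96), gives:

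| N | 10% | 12% | 15% |
|---|---|---|---|
| 160 | 71.6% | 85.9% | 96.7% |
| 200 | 80.7% | 92.4% | 98.9% |
| 250 | 88.5% | 96.7% | 99.7% |

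Only N = 200 matches all three printed figures. This is an inference about how they arose, but it supports reading them as power for 200 analysed participants.

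**5. Power for the comparison the design makes.** For two proportions with pooled variance under the null, assumed two-sided 5%:

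power = Phi[(d - 1.96 x sqrt(2 x pbar x (1 - pbar)/n)) / sqrt((p1(1 - p1) + p2(1 - p2))/n)]

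With p1 = 0.05, p2 = 0.15, pbar = 0.10:

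- n = 100: (0.10 - 1.96 x 0.0424)/0.0418 = 0.40, power about 66%.
- n = 80: (0.10 - 1.96 x 0.0474)/0.0468 = 0.15, power about 56%.

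Over a range of assumed control rates:

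| Difference | n per arm | Control 5% | Control 10% | Control 30% |
|---|---|---|---|---|
| 10 points | 100 | 66% | 51% | 32% |
| 10 points | 80 | 56% | 42% | 26% |
| 15 points | 100 | 90% | 80% | 59% |
| 15 points | 80 | 83% | 71% | 50% |

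For 10 points, going from 100 to 80 per arm costs about 5 to 10 percentage points of power. The gap between the printed 81% and the value at 100 per arm is larger: 15, 30 and 49 points at the three control rates. At 100 per arm, no control rate between 0.1% and 84.9% reproduces all three printed figures.

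**The case against.** The strongest reply is that the Sample Size section settles the matter. It holds the only recruitment endpoint in the article, its arithmetic is right, and nothing says recruitment ends at 200. The abstract and introduction could be taken as shorthand for the evaluable sample. Most of this stands. Whoever follows Sample Size, with all 250 randomised, has no shortfall. What does not stand is the shorthand: the Objective and the Introduction apply 200 to randomisation in so many words, and nothing in the article says that it means completers.

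Four stronger readings are tempting, and the document does not support them.

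- A reader might infer that the trial will end with 160 analysable participants. That requires stopping at 200, which the article nowhere plans, and the full 20% loss, which it calls generous.
- A reader might see a contradiction inside Sample Size, between enrolling and maintaining 200 and recruiting 250. Read on, the section presents the 250 as the means of keeping 200, so it explains itself.
- A reader might count the Study Overview and the Abstract's methods as further statements of the number randomised. They give a trial size only. They should be aligned, but they are weaker evidence.
- A reader might conclude that writing 250 makes the printed power sound. It does not: at 100 per arm the two-arm power is already well below 81% at each control rate tabulated.

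**Conclusion.** The inconsistency is real and concerns a figure the trial relies on, but it is one of wording, not of calculation. About 200 randomised (Objective, Introduction) and about 250 enrolled to leave 200 completing (Sample Size) cannot both be right at 20% loss. The possible consequence is 160 completers, or 180 to 190 at the cited retention, in place of 200, and only if recruitment stops at 200 randomised. The counts rest on the article's own figures. The power figures rest on an assumed two-sided 5% alpha and assumed control rates. They show that the counts and the power statement both need correcting, and that correcting the first does not repair the second.

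**What to change.** State one set of figures wherever the trial size appears: about 250 randomised (125 per arm), with about 200 (100 per arm) expected to complete. Bring the Abstract (objective and methods), the Introduction and the Study Overview into line with Sample Size. In Sample Size, say that the 250 counts randomised participants, since registration and the baseline survey come before randomisation.

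If recruitment will in fact stop at 200 randomised, say so and give about 160 expected completers (about 80 per arm).

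In either case, recompute the power for the expected completers per arm, and state alpha, sidedness and the assumed control-arm testing rate.

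Aligning the counts costs only wording. If enrolment has been counted at registration, reaching 250 randomised may need somewhat more recruitment. Restating the power takes one short calculation, and the result will probably be less favourable than the printed figures.

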### Trial Registration, Ethics, Consent, and Institutional Board Approval

The Institutional Review Board of the University of Michigan has approved this study (HUM00102906). The study has also been registered on ClincalTrials.gov (NCT03185975). The samples will be reflective of the racial and ethnic diversity of the United States and are deemed to pose no more than minimal risk to the participants.

## Results

Project Moxie began recruitment on June 19, 2017 and has enrolled 130 participants as of August 21, 2017. Self-testing kits have been mailed to a total of 71 participants. Video-chat sessions for 12 participants randomized to the experimental arm have been completed and 58 participants from the control arm have entered their test results into the study database.

## Discussion

Telehealth-based HIV counseling provides TY the opportunity to test for HIV in a comfortable and safe space, as well as problem-solve issues related to testing and risk behavior that are specific to their life experiences. This approach also provides a point of care to TY residing in areas where gender-affirming health care may be scarce, and provides a space free of the discrimination and harassment TY often encounter while trying to access health care resources.

A potential limitation is the protocol’s reliance on existing health care resources for linkage to care and follow-up. TY may participate in Project Moxie due to a lack of locally-available resources that are accepting and gender-affirming. However, after their initial session, those who test positive and/or require additional services may find limited options in their local area and may have difficulty entering into the continuum of care. The current price of self-test kits (approximately US $30-40) may be prohibitive for many TY and could be a barrier to routine testing in areas without gender-affirming or subsidized HIV testing services.

Despite these limitations, pairing HIV testing with counseling and linkage to care is an innovative approach to increasing access to sexual health care. Using telehealth to link high-risk TY to HIV testing and care has the potential to reduce the high rate of HIV and STI transmission among this high-risk and often-marginalized population.

## Abbreviations

CDC: Centers for Disease Control and Prevention
CSQ-8: Client Satisfaction Questionnaire
GEE: generalized estimating equation
GMSRS: Gender Minority Stress and Resilience Scale
HIPAA: Health Information Portability and Accountability Act
HIV: human immunodeficiency virus
ID: identification
LGBT: lesbian, gay, bisexual, transgender
MSM: men who have sex with men
PrEP: preexposure prophylaxis
RCT: randomized controlled trial
SEF: Self-Evaluation Form
SMS: short message service
STI: sexually transmitted infection
TY: transgender and gender nonconforming youth
